# A healthy diet with and without cereal grains and dairy products in patients with type 2 diabetes: study protocol for a random-order cross-over pilot study - Alimentation and Diabetes in Lanzarote -ADILAN

**DOI:** 10.1186/1745-6215-15-2

**Published:** 2014-01-02

**Keywords:** Protocol, Random-order cross-over trial, Type 2 diabetes mellitus, Metabolic diseases, Dietary intervention, Grain-free diet, Dairy-free diet, Glucagon, Fructosamine

## Abstract

**Background:**

Research on the role of nutrition in type 2 diabetes has largely focused on macro/micronutrient composition and dietary fiber intake, while fewer studies have tested the effects of differing food choice. Some observational studies and short-term intervention studies suggest that a food pattern mimicking the diet with which humans evolved positively influences glucose control and associated endocrine systems. Such a food pattern mainly differs from other common healthy food patterns in its absence of cereal grains and dairy products. The primary aim of this pilot study is to determine the effect of two healthy diets with or without cereal grains and dairy products on glucose control, while keeping participants’ weight stable and other food parameters, such as macro/micronutrient composition, dietary fiber and glycemic load, the same in both diets.

**Methods/Design:**

We intend to include 15 adult patients with a medical diagnosis of type 2 diabetes mellitus with or without medication and with an increased waist circumference (≥ 80 cm for women and ≥ 94 cm for men) in a random-order cross-over diet intervention study during two periods of four-weeks separated by a six-week washout period. Patients will be instructed to eat two healthy diets according to official dietary guidelines with respect to macro/micronutrient composition and fiber content, but differing in the type of food included, with one diet being without cereal grains and dairy products. Lunch will be served in a hospital kitchen for control of nutrient intake, while the rest of the meals will be eaten at home according to specific directions. The energy content of the diets will be individually adjusted to maintain a stable body weight during the two four-week intervention periods. Primary outcomes will be change in fasting plasma glucagon and fructosamine, while secondary outcomes include change in fasting glucose and glycated hemoglobin, glucose and glucagon response during oral glucose tolerance test, blood lipids, blood pressure, C-reactive protein, body composition, quality of life, subjective experience with the two diets, satiety scores and changes in medication.

**Discussion:**

Using these results, we will assess the need to conduct larger and longer studies with similar design.

**Trial registration:**

This trial was registered at clinicaltrials.gov as NCT01891955 and Spanish Agency of Medication and Sanitary Products (AEMPS) registration code: MFV-ADI-2013-01.

## Background

The prevalence of type 2 diabetes mellitus (T2DM) has increased dramatically (more than doubled) since 1980, with a global prevalence of 9.8% and 9.25% for men and women, respectively, and affecting 347 million adults in 2008 [1]. In Europe, the prevalence of T2DM is estimated to be 8.1% of the adult population, affecting 52.8 million people in 2011. The estimated prevalence of T2DM for 2030 is 9.5% of the adult population affecting 64.2 million people. T2DM accounts for 85 to 90% of all cases of diabetes mellitus.

T2DM is one of the world’s most important causes of mortality, disability and economic cost due to the associated increase in the risk of micro- [2] and macrovascular [3] complications. T2DM caused 282,400 and 317,000 deaths in 2011, for men and women, respectively [4]. Estimates indicate that at least USD 131 million were spent in Europe due to T2DM in 2011 [4]. In 2003, the prevalence of T2DM in the archipelago of Canary Islands (Spain) was estimated to be 12% of the population with an economic cost of €38.8 million, which accounts for 2.1% of all the health costs of the Canary Islands’ Government [5,6]. Furthermore, micro- and macrovascular complications, including end-stage renal disease, are four to five times higher than in the rest of Spain [6,7]. In impaired glucose tolerance (IGT), lifestyle intervention reduces the incidence of T2DM [8], even when compared with insulin sensitizing medication [9]. In a study from primary health care in Stockholm, more cardiovascular risk factors were improved after an exercise intervention in people with normal glucose tolerance compared with those with IGT or T2DM [10]. However, in these studies the separate effect of exercise versus diet could not be elucidated [11]. Data from systematic reviews regarding the role of food in the prevention and treatment of T2DM indicates that there are some uncertainties with respect to the optimal dietary intervention [11,12], and results from one large interventional dietary study suggest that targeting macronutrient composition by lowering total fat intake and increasing carbohydrate intake from whole grains, may have detrimental effects in women with pre-existing T2DM [13]. A recent intensive diet and exercise program in patients with T2DM was stopped because the intervention did not reduce cardiovascular risk, despite significant weight loss at four years, compared to the control group [14]. Research on the role of nutrition in T2DM has largely focused on macro/micronutrient composition and fiber intake, while fewer studies have tested the more direct endocrine effects of food [13,15,16]. A recent systematic review and meta-analysis suggests that low-carbohydrate, low-glycemic index, Mediterranean and high-protein diets may be effective in improving cardiovascular disease risk and diabetes management compared to control diets, with no significant difference effect between the different interventions [17]. Also, the effect of weight loss over macronutrient composition precludes drawing a definitive conclusion derived from this meta-analysis.

Theoretically, dietary interventions can improve glucagon [18] and leptin physiology [19]. Thus, we speculate that the possible effects of the diets in the ADILAN study could be mediated, in part, by improving the action of those hormones.

Some observational studies [20] and two short-term intervention trials from our group [21,22] suggest that a food pattern mimicking the diet with which humans evolved, may be an optimal approach for patients with T2DM. Importantly, the short-term trials compared the experimental approach to the recommended dietary treatment in each case, namely the Mediterranean diet for patients with ischemic heart disease [21] and the American Diabetes Association diet for patients with T2DM [22], respectively. In both trials, the experimental approach resulted in better outcomes than in the control diet. A noteworthy finding in those dietary trials is the significant difference in reported macronutrient composition between interventions and controls, specifically, higher energy percentage intake for protein and fat (except in Lindeberg *et al*. [21] for fat), and lower energy percentage intake for carbohydrate in the experimental versus the control diet, taking into account that the intervention diet was not fixed to any dietary macronutrient ratio. Dietary glycemic load (GL) was also significantly lower.

Notwithstanding these findings, the beneficial effects shown in the experimental diets in both trials are not fully explained by macronutrient composition or GL after further statistical analysis [21,22]. We concluded that food choice, rather than micro-and macronutrient composition, may have been the most important factor leading to the beneficial effects observed. In a recent meta-analysis comparing Mediterranean diets to alternative dietary strategies, the authors stated that the paleolithic diet (a healthy diet without grains and dairy) in the study by Lindeberg *et al*. [21] demonstrated the most positive effect on fasting blood glucose of all the studies included in the meta-analysis [23].

### The Alimentation and Diabetes in Lanzarote (ADILAN) study

The major aim of the ADILAN study is to test the direct endocrine effect of food items beyond macro/micronutrient composition, fiber content and glycemic load of the diet. For this purpose, we will try to avoid weight loss in an attempt to isolate the effect of food, as weight loss could have been a confounding factor in the previous studies. Our objective is to run a pilot intervention for a later long-term study with a representative sample in patients with T2DM. The working hypothesis is that food choice rather than macro/micronutrient composition, fiber intake, or GL, is a major determinant for the prevention and treatment of T2DM. Hypothetically, the foods that composed the diet during most of the time of *Homo sapiens*’ evolution, may be the optimal dietary approach for the prevention and treatment of T2DM [24,25].

## Methods/Design

### Participants

We aim to enroll 15 participants with T2DM, males and females, > 18 years old based, on the power calculations (see below) estimation of a required minimum of 13 patients, allowing for one or two drop-outs. Patients live in the island of Lanzarote, in the archipelago of Canary Islands (Spain), located off the western coast of Africa.

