### Power calculations

The predefined primary outcomes are changes in fasting fructosamine and glucagon. In order to detect, with 80% power and at a significance level of 5%, a 26 μmol/L larger reduction in fructosamine after diet B than after diet A, 12 subjects are estimated to be required. For a 37 ng/L difference in change in fasting glucagon between the diets, 13 subjects are estimated to be required.

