#### Improving patients adherence to the meal plan

Despite the notion that a healthy diet can improve glucose control, adherence to dietary advice is generally poor among patients with T2DM [31]. Moreover, the particular dietary design of this trial could increase the risk of nonadherence. In order to minimize this risk, several strategies will be adopted. To facilitate the participants eating the same approximate amount of equivalent food in every meal (expressed in grams in Additional file 3), we will supply a table of equivalence. For example, 56 grams of tinned tuna equates to a small tin of tuna and 20 grams of bread corresponds to a slice of bread. Similarly, food items such as eggs or fruits will be listed as small, medium or large. In the case of more elaborated dishes, such as stewed meat, baked tubers, soups, or creams, we will provide the participants with detailed recipe directions corresponding to four servings, so as to facilitate the task in the family context. On the first day of each intervention, the investigators will review all the assigned meals, together with the participants and their partners, to make sure that the directions are understandable and easy to follow. Previous to starting the study, subjects not included in the trial will test the meals in order to elaborate a meal plan that is understandable and easy. We will ask the participants to call one of the investigators if they have any questions regarding the meal plan. Besides this, one of the investigators will meet the participants in the lunch room at the beginning of each week to give behavioral support. Furthermore, an assistant will be present on a daily basis in the lunch room to ensure that the meals are served as planned. Also, the assistant will be asked everyday to inquire whether the participants have any difficulties following the meal plans.

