### Dietary design

The main goal of the study is to test the hypothesis that the type of food has an effect on glucose control, independently of macro/micronutrient composition, fiber content, GL and weight loss. Therefore, we generated two different seven-day meal patterns where macro/micronutrient composition and fiber intake are similar. GL is also similar between both seven-day meal patterns. Furthermore, we aim at creating two healthy food patterns, according to official nutritional guidelines in Canary Islands, utilizing a validated nutritional software package (DIAL) [32]. The nutritional composition of the menu plan was analyzed using another validated nutritional software (Dietist XP 3.1; Kost och Näringsdata AB, Bromma, Sweden) to check for possible errors. Minimal differences were observed in the results from both programs. The distribution of macronutrient energy of diets is 19% protein, 28% fat and 53% carbohydrate, and 18% protein, 28% fat, and 53% carbohydrate for healthy diet A and healthy diet B, respectively. The amount of fiber per 2,000 kcal is approximately 48.5 g and 53.1 g in healthy diet A and healthy diet B, respectively. The GL per 2,000 kcal is 116 and 118 in healthy diet A and healthy diet B, respectively. Regarding micronutrient intake, significant differences between the two diets can be seen in Table 2. Importantly, and because one goal of the ADILAN trial is to avoid weight loss, dried fruits were regularly included instead of fresh fruits, in healthy diet B, to match the total weight of food between the two food patterns. Two recent studies have shown that substituting cereal grains for fruits and vegetables increases satiety [19,33], and therefore it may be challenging for the participants to avoid weight loss while adhering to healthy diet B.

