### Data analysis

Differences in baseline characteristics between the participants will be measured using two-tailed unpaired *t*-tests. A two-tailed paired *t*-test will be used to analyze treatment effects within subjects and a two-tailed unpaired *t*-test will be used to compare mean values of outcome variables between the two diets. Normal Q-Q plots and Shapiro-Wilk test will be performed to check for normal distribution of data. Data transformation will be applied in case the data does not present normal distribution. To test for a possible period effect a two-tailed unpaired *t*-test comparing the mean difference between first and second period for outcome variables and food intake will be performed. To test a possible carry-over effect a two-tailed unpaired *t*-test comparing the average of observations for outcome variables and food intake between the two periods will be performed. *P* < 0.05 will be considered to indicate statistical significance.

Analysis will be conducted by use of SPSS for Mac Version 20 (IBM SPSS Statistics for Mac, Version 20.0. Armonk, NY: IBM Corp.)

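### With one or two of 15 participants expected to drop out, neither t-test named for the diet comparison makes good use of someone who completes only one period

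*Protocol article*

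**What the plan says.** The Participants section enrols 15 people, based on an "estimation of a required minimum of 13 patients, allowing for one or two drop-outs". The Power calculations section gives the two figures behind that minimum. For fructosamine it is "a 26 μmol/L larger reduction in fructosamine after diet B than after diet A, 12 subjects are estimated to be required". For glucagon it is "For a 37 ng/L difference in change in fasting glucagon between the diets, 13 subjects are estimated to be required".

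Both primary outcomes are measured fasting at the start and end of each four-week period (Primary outcomes). Someone who leaves after period 1 or during the six-week washout therefore already has a complete change score for one diet.

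For the treatment effect, the Data analysis section names two tests. A two-tailed paired t-test "will be used to analyze treatment effects within subjects", and a two-tailed unpaired t-test compares outcome means between the two diets. The section does not say which of them carries the primary diet contrast.

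Two other sections bear on retention. The section on adherence warns that "the particular dietary design of this trial could increase the risk of nonadherence". Dietary design notes that "it may be challenging for the participants to avoid weight loss while adhering to healthy diet B". The trial is open label for participants, staff and outcome assessors (Intervention).

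**The concern.** The sizing expects one or two incomplete participants, yet the two named tests treat such a person differently and neither does so well.

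- **Paired A-versus-B test.** No within-person difference can be formed from one period, so the person is dropped and a complete period-1 change is lost. The result rests on those who finished both diets.
- **Unpaired test.** The person stays in under one diet with no counterpart under the other. The test treats the two diets' values as coming from different people, which gives up the main advantage of a cross-over.

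If leaving depends on how someone responded in period 1, the two tests can be biased in different directions by the same departures. At stake is a modest distortion of the primary contrast in a small pilot whose results will be used to judge the need for larger and longer trials.

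**Working it through.** **1. The plan's own figure.** 13 / (1 − 2/15) = 15, so enrolment of 15 reproduces. The expected loss is 1/15 = 6.7% to 2/15 = 13.3%.

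**2. Implied variability (an assumption).** The article gives no SD. Solving a two-sided 5% paired t-test with 80% power, n = 12 and a difference of 26 μmol/L gives an SD of the within-person difference of 29.3 μmol/L. For n = 13 and 37 ng/L it gives 43.7 ng/L. These are the largest SDs consistent with the stated sample sizes.

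**3. Who each test uses.** With 15 randomised and two people having one period only, on the same diet:
- paired: 13 pairs, 12 degrees of freedom;
- unpaired: 15 versus 13 values, 26 degrees of freedom.

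**4. Cost of ignoring pairing.** If a person's two changes have correlation ρ, the SD of a single change is s = SD_diff / √(2(1 − ρ)). At SD_diff = 29.3 this is 20.7 for ρ = 0 and 37.8 for ρ = 0.7. The unpaired test is judged against s, so its power falls as ρ rises, while paired power depends only on SD_diff.

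| Outcome | Paired, 13 completers | Unpaired 15 v 13, ρ = 0 | Unpaired 15 v 13, ρ = 0.7 |
|---|---|---|---|
| Fructosamine, 26 μmol/L | 83.6% | 89% | 42% |
| Glucagon, 37 ng/L | 80.0% | 86% | 38% |

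**5. Direction of bias in an adverse case.** Assume no true diet effect, and suppose the two worst period-1 responders among diet-B starters leave after period 1. Let m be their mean diet-B change (positive means a worse result). Their expected diet-A change would have been ρm. For B minus A, where a negative value favours diet B:
- paired, 13 completers: shift = −2m(1 − ρ)/13;
- unpaired, 15 v 13: the diet-B mean is unaffected and the diet-A mean loses two values expected at ρm, so shift = +2ρm/13.

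The signs are opposite for any positive ρ, and the ratio of sizes is ρ/(1 − ρ).

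**6. Size by simulation** (15 people, no diet effect, two such drop-outs):

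| ρ | Paired: towards B (μmol/L) | Paired rejection | Unpaired: against B (μmol/L) | Unpaired rejection |
|---|---|---|---|---|
| 0 | 3.6 | 7.4% | about 0 | 5.0% |
| 0.3 | 3.0 | 6.6% | 1.2 | 2.5% |
| 0.5 | 2.4 | 5.9% | 2.5 | 1.2% |

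The ratios agree with step 5: at ρ = 0.3, 0.3/0.7 = 0.43 against 1.2/3.0 = 0.40; at ρ = 0.5, 1 against 2.5/2.4 = 1.04. A separate run over ρ from 0 to 0.7 gave 3.7 down to 1.9 towards diet B for the paired test. For the unpaired test it gave about 0 up to 4.7 against diet B, with rejection falling to about 0.3%. With one such drop-out, the paired shift is 1.5 to 2.0 μmol/L for ρ = 0.5 down to 0.

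**7. Scale.** Against the 26 μmol/L target, the paired shift is 1.9/26 = 7% to 3.7/26 = 14%, and the unpaired shift is at most 4.7/26 = 18%. The paired standard error with 13 completers is about 29.3/√13 = 8.1 μmol/L, so the paired shift is 1.9/8.1 = 0.23 to 3.7/8.1 = 0.46 standard errors.

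**8. The alternative.** In the same adverse case, a REML mixed model with the correlation estimated from the data stayed within about 0.6 μmol/L of zero, with rejection of 4% to 6%.

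**The case against.** The strongest objection is that the unpaired test, which the Data analysis section assigns to comparing the diets, does accept one-period participants. A reader might infer that the named t-tests cannot use such a person at all, or that the diet contrast necessarily rests on those who tolerated both diets. The text does not support either. The paired test may even be meant for start versus end of a period, which can also use one-period data. This stands, and it confines the completer problem to a paired diet contrast. It does not rescue the unpaired test, which gives up the pairing and can be biased the other way.

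A reader might also infer that the plan is tilted towards diet B. The documents do not support that either. The adherence passage concerns non-adherence and is followed by measures to reduce it. The remark about diet B concerns unwanted weight loss, not withdrawal or poor glycaemic response. If the two best diet-B starters left instead, the paired shift would be 2.6 to 3.4 μmol/L against diet B. If one person left from each sequence, or the two worst responders left regardless of diet, it would be about zero. So the direction is unknown.

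The Consent section keeps a queue of reserves, and some of the loss might precede randomisation, since the first 15 enrolled are tested before final inclusion. Both points are fair. But a replacement restores numbers, not the departed person's data, and the Intervention section has everyone starting together.

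Finally, a rule for incomplete participants may sit in a fuller document, and its absence from the article is not the criticism. The criticism is of the tests that the article does name. That this is a pilot and the effect is small also stands, and it limits the weight of the point.

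**Conclusion.** The point holds in a limited form. The plan expects 6.7% to 13.3% of participants to be lost, and both named t-tests are poor choices for someone with one completed period. The paired contrast discards usable data. The unpaired one ignores pairing and, at ρ = 0.7, would have about 38% power for glucagon. In the adverse case the two are biased in opposite directions at positive correlation: about 2 to 3.7 μmol/L towards diet B (paired) and about 0 to 4.7 μmol/L against it (unpaired).

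These sizes rest on a back-solved SD, an assumed correlation of 0 to 0.7, and an assumed pattern in which the two worst diet-B starters leave after completing period 1. Drop-out unrelated to response gives no bias. The change is worth making because it is cheap and performs better than both named tests. Confidence that the problem would materially alter this trial's result is low.

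**What to change.** In the Data analysis section, make the primary diet comparison, for change in fructosamine and change in glucagon, a linear mixed model fitted by REML. Use diet and period as fixed effects, participant as a random effect, and a small-sample method for the degrees of freedom. Fit it to every randomised participant with at least one completed period, so that someone who leaves after period 1 contributes that change. Keep the paired analysis of those who complete both periods as a sensitivity analysis. Report drop-outs by the diet being eaten when they left. This also settles which analysis carries the primary contrast.

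The cost is a change of wording. It needs no extra participants or measurements, and the named software, SPSS 20, can fit the model. There are two limits. The model is valid only if drop-out is explained by the observed data. It also cannot recover anyone who leaves during a period without an end-of-period value, such as a diet-B starter who stops midway through period 1.

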### Recruitment

Patients will be recruited through different strategies. We are in collaboration with the *Asociación de Diabéticos de Lanzarote* (ADILA), a local organization, whose aim is helping patients to deal with the consequences of type 1 diabetes and T2DM. Data from 1996 estimated the prevalence of T2DM in Lanzarote to be 6.6% of the population aged between 15 and 75 years old, with an absolute number of 4,067 patients [26,27]. ADILA will contact the potential participants registered in their database by telephone, Email and advertisement in the association’s bulletin board. In addition, we will advertise the study in the local newspapers, radio and in some institutional websites on the island of Lanzarote. Patients interested in participating in the study will receive general oral and/or written information about the study. They will be informed that our objective is to compare two healthy diets because we do not know which, if any, is the better one. If a person is interested, we will register their name and telephone number for further contact. After recruiting 15 potential participants, a meeting will be arranged to provide further details about the study.

